**Figure 5-1 Arm A and B Dose Regimen 1**

[figure not shown]

Subjects enrolled in Arm A and B DR 1 will receive Course 1 consisting of DL 1 on Weeks 1, 2, and 3 followed by a rest during Week 4, with clinical evaluations.

Course 2 will commence for subjects without DLT and who meet criteria for subsequent CAR T cell infusions (Section 5.5.2 Requirements for subsequent CAR T cell infusion and dose modification). Subjects will receive DL 1 on Week 1, DL 2 on Weeks 2 and 3, followed by a rest during Week 4 with disease evaluation, including radiographic restaging.

Following Course 2, subjects meeting criteria for further CAR T cell infusion (Section 5.5.2) may receive additional Courses of therapy until subject meets criteria for removal from protocol therapy, intolerable toxicity, or depletion of available manufactured CAR T cells. The DLs for Courses 3 and beyond will be no higher than DL 2 or the dose which no DLTs were experienced by the subject during Courses 1 and 2. A lower DL may be administered based on availability of CAR T cells, see Section 5.1.2 Dose Regimen assignment. Treatment will be administered on Weeks 1, 2, and 3 followed by a rest week every fourth week. Disease restaging evaluations will occur as indicated in the schedule of procedures.

**Figure 5-2 Arm A and B Dose Regimen 2**

[figure not shown]

Subjects enrolled in Arm A and B DR 2 will receive Course 1 consisting of DL 1 on Week 1, DL 2 on Weeks 2 and 3 followed by a rest during Week 4, with clinical evaluations.

Course 2 will commence for subjects meeting criteria for subsequent CAR T cell infusion (Section 5.5.2). Subjects will receive DL 2 on Week 1, DL 3 on Weeks 2 and 3, followed by a rest during Week 4 with disease evaluation, including radiographic restaging.

Following Course 2, subjects meeting criteria for further CAR T cell infusion (Section 5.5.2) may receive additional Courses of therapy until subject meets criteria for removal from protocol therapy, intolerable toxicity, or depletion of available manufactured CAR T cells. The DLs for Courses 3 and beyond will be no higher than DL 3 or the dose at which no DLTs were experienced by the subject during Courses 1 and 2. A lower DL may be administered based on availability of CAR T cells, see Section 5.1.2 Dose Regimen assignment. Treatment will be administered on Weeks 1, 2, and 3 followed by a rest week every fourth week. Disease restaging evaluations will occur as indicated in the schedule of procedures.

**Figure 5-3 Arm A and B Dose Regimen 3**

[figure not shown]

Subjects enrolled in Arm A and B DR 3 will receive Course 1 consisting of DL 1 on Week 1, DL 3 on Weeks 2 and 3 followed by a rest during Week 4, with clinical evaluations.

Course 2 will commence for subjects meeting criteria for subsequent CAR T cell infusion (Section 5.5.2). Subjects will receive DL 3 on Week 1, DL 4 on Weeks 2 and 3, followed by a rest during Week 4 with disease evaluation, including radiographic restaging.

Following Course 2, subjects meeting criteria for further CAR T cell infusion (Section 5.5.2) may receive additional Courses of therapy until subject meets criteria for removal from protocol therapy, intolerable toxicity, or depletion of available manufactured CAR T cells. The DLs for Courses 3 and beyond will be no higher than DL 4 or the dose at which no DLTs were experienced by the subject during Courses 1 and 2. A lower DL may be administered based on availability of CAR T cells, see Section 5.1.2 Dose Regimen assignment. Treatment will be administered on Weeks 1, 2, and 3 followed by a rest week every fourth week. Disease restaging evaluations will occur as indicated in the schedule of procedures.

### 5.1.5 Arm C Dose Regimens 1 through 4

**Figure 5-4 Arm C Dose Regimen 1**

[figure not shown]

Subjects enrolled in Arm C DR1 will receive Course 1 consisting of DL 1 on Weeks 1 and 3 followed by a rest during Week 4, with clinical evaluations.

Course 2 will commence for subjects without DLT and who meet criteria for subsequent CAR T cell infusions (Section 5.5.2). Subjects will receive DL 1 on Week 1 and DL 1 on Week 3, followed by a rest during Week 4 with disease evaluation, including radiographic restaging.

Following Course 2, subjects meeting criteria for further CAR T cell infusion (Section 5.5.2) may receive additional Courses of therapy until subject meets criteria for removal from protocol therapy, intolerable toxicity, or depletion of available manufactured CAR T cells. The DLs for Courses 3 and beyond will be no higher than DL 1 unless a subsequent DR has been cleared for escalation or for selection as the MTDR. In that case, the subject may increase to the highest DL on the subsequent DR. Treatment will be administered on Weeks 1 and 3 followed by a rest week every fourth week. Disease restaging evaluations will occur as indicated in the schedule of procedures.

**Figure 5-5 Arm C Dose Regimen 2**

[figure not shown]

Subjects enrolled in Arm C DR 2 will receive Course 1 consisting of DL 1 on Weeks 1 and 3 followed by a rest during Week 4, with clinical evaluations.

Course 2 will commence for subjects without DLT and who meet criteria for subsequent CAR T cell infusions (Section 5.5.2). Subjects will receive DL 2 on Weeks 1 and 3, followed by a rest during Week 4 with disease evaluation, including radiographic restaging.

Following Course 2, subjects meeting criteria for further CAR T cell infusion (Section 5.5.2) may receive additional Courses of therapy until subject meets criteria for removal from protocol therapy, intolerable toxicity, or depletion of available manufactured CAR T cells. The DLs for Courses 3 and beyond will be no higher than DL2 or the dose at which no DLTs were experienced by the subject during Courses 1 and 2 unless the subject did not experience a DLT and a subsequent DR has been cleared for escalation or for selection as the MTDR. If that occurs, then the DL may increase to the highest DL on the cleared DR. A lower DL may be administered based on availability of CAR T cells, see Section 5.1.2 Dose Regimen assignment.

Treatment will be administered on Weeks 1 and 3 followed by a rest week every fourth week. Disease restaging evaluations will occur as indicated in the schedule of procedures.

**Figure 5-6 Arm C Dose Regimen 3**

[figure not shown]

Subjects enrolled in Arm C DR 3 will receive Course 1 consisting of DL 1 on Week 1 and DL 2 on Week 3 followed by a rest during Week 4, with clinical evaluations.

Course 2 will commence for subjects meeting criteria for subsequent CAR T cell infusion (Section 5.5.2). Subjects will receive DL 3 on Weeks 1 and 3, followed by a rest during Week 4 with disease evaluation, including radiographic restaging.

Following Course 2, subjects meeting criteria for further CAR T cell infusion (Section 5.5.2) may receive additional Courses of therapy until subject meets criteria for removal from protocol therapy, intolerable toxicity, or depletion of available manufactured CAR T cells. The DLs for Courses 3 and beyond will be no higher than DL 3 or the dose at which no DLTs were experienced by the subject during Courses 1 and 2 unless a subsequent DR has been cleared for escalation or for selection as the MTDR. If that occurs, then the DL may increase to the highest DL on the cleared DR. A lower DL may be administered based on availability of CAR T cells, see Section 5.1.2 Dose Regimen assignment. Treatment will be administered on Weeks 1 and 3 followed by a rest week every fourth week. Disease restaging evaluations will occur as indicated in the schedule of procedures.

**Figure 5-7 Arm C Dose Regimen 4**

[figure not shown]

Subjects enrolled in Arm C DR 4 will receive Course 1 consisting of DL 1 on Week 1 and DL 3 on Week 3 followed by a rest during Week 4, with clinical evaluations.

Course 2 will commence for subjects meeting criteria for subsequent CAR T cell infusion (Section 5.5.2). Subjects will receive DL 4 on Weeks 1 and 3, followed by a rest during Week 4 with disease evaluation, including radiographic restaging.

Following Course 2, subjects meeting criteria for further CAR T cell infusion (Section 5.5.2) may receive additional Courses of therapy until subject meets criteria for removal from protocol therapy, intolerable toxicity, or depletion of available manufactured CAR T cells. The DLs for Courses 3 and beyond will be no higher than DL 4 or the dose at which no DLTs were experienced by the subject during Courses 1 and 2. A lower DL may be administered based on availability of CAR T cells, see Section 5.1.2 Dose Regimen assignment.

Treatment will be administered on Weeks 1 and 3 followed by a rest week every fourth week. Disease restaging evaluations will occur as indicated in the schedule of procedures.

### 5.1.6 Treatment Plan Delays

During each Course, the time interval between each CAR T cell infusion will be according to the Schedule of Procedures and based upon the date of the most recent CAR T cell infusion. The end date of each Course will be the date of completion of Week 4 evaluations per the Schedule of Procedures. The start date of each Course will be the date that the Week 1 CAR T cell infusion required evaluations are performed.

Within Course 1 and 2, if a subject does not meet the criteria to receive a CAR T cell infusion ([Section 5.5.2](#)) on the planned infusion day of a Course regardless of attribution to the CAR T cells, the infusion may be delayed no more than 3 weeks from the planned infusion date. If delayed greater than 3 weeks from the planned infusion date, the subject will be removed from

protocol therapy and will not receive further CAR T cell treatment. See [Section 8.1](#) Removal from Protocol Therapy.

Between Course 2 and Course 3, delays due to family/subject preference, investigator discretion, or due to subject recovery from a surgical procedure (e.g., tumor biopsy) are allowed. Following Course 3, only delays due to subject recovery from a surgical procedure (e.g., tumor biopsy) or due to travel disruptions are allowed. During the delay subjects must continue to be followed for concomitant medications (Section 7.8) and adverse events (Section 7.9). Criteria for removal from protocol therapy in Sections 5.5.2 and 8.1 will override family/subject/investigator preference delays as noted above.

Beyond Course 2, subjects must receive at least the Week 1 infusion of any Course but may skip the other scheduled infusions. If a subject does not receive an infusion within 3 weeks of the Week 1 infusion, the next infusion will be considered a new Course. If infusions are delayed, the subsequent pre- and post-visit evaluations/procedures (see [Appendix 2 – Schedule of Procedures](#)) will be timed based upon the next administered CAR T cell infusion. If an infusion is not given, the pre- and post-visit procedures for that infusion are not required. If delay to subsequent infusion is greater than 8 weeks from prior infusion, disease response assessment must be obtained prior to dosing.

## 5.2 Dose-Limiting Toxicity (DLT)

A DLT is an event, defined below, which, in the opinion of the investigator, is possibly, probably, or definitely attributable to the CAR T cell product and which occurs from the time of initial CAR T cell infusion through 28 days following the final CAR T cell infusion. The Maximum Tolerated Dose Regimen (MTDR) will be established by the occurrence of DLTs which occur from the time of initial CAR T cell infusion through 7 days following the final CAR T cell infusion received during Course 2. See Section 9.9.4 Definition and determination of MTDR and RP2DR, for information on establishing MTDR.

The definition of a DLT includes all  $\geq$  Grade 3 Common Terminology for AEs (CTCAE) v5 toxicities **except**  $\geq$  Grade 3 toxicities that are known to be related to CAR T cells [45], listed below.

Exceptions to  $\geq$  Grade 3 DLTs:

- Grade 3 CRS that decreases to  $\leq$  Grade 2 within 72 hours of onset
- $\geq$  Grade 3 hypotension, fever, chills not controlled with medical intervention that decrease to  $\leq$  Grade 2 within 72 hours
- $\geq$  Grade 3 activated PTT, fibrinogen, and/or INR that are asymptomatic and resolve within 72 hours
- $\geq$  Grade 3 hypoglycemia and/or electrolyte imbalance that are asymptomatic and resolve within 72 hours
- $\geq$  Grade 3 nausea and/or vomiting that decrease to  $\leq$  Grade 2 within 7 days

- Arm A and B only: Grade 3 neurological adverse event that decreases to  $\leq$  Grade 2 within 7 days
- Arm C only: Grade 3 neurological adverse event that decreases to  $\leq$  Grade 2 within 21 days (treatment with dexamethasone and/or bevacizumab is allowed)

The definition of a DLT also includes any related toxicity lasting  $> 14$  days which prohibits the subject from meeting criteria for subsequent CAR T cell infusion.

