#### **9.5 Safety and Tolerability**

Subjects receiving any CAR T cell product will be eligible for safety and tolerability analyses. If a subject is removed from study prior to receiving the initial CAR T cell infusion, they will be replaced. For the purpose of assessing overall safety and tolerability, subjects will be evaluated for toxicities for up to 28 days following final CAR T cell infusion. For the purposes of escalation of DR and defining Maximal Tolerated Dose Regimen (MTDR), subjects in the existing cohort will be evaluated for toxicities from the time of initial CAR T cell infusion through 7 days following the final CAR T cell infusion received during Course 2, or until they commence with alternate therapies for their CNS tumor, whichever comes first. Subjects who are taken off study prior to Day 28 of Course 2 and have experienced a DLT will count towards that DR's evaluable accrual and will not be replaced. For all Arms, if a subject is removed from study prior to Day 28 of Course 2 for reasons other than toxicity (e.g., progressive disease requiring immediate alternative therapy) and has not received at least one dose of the maximally intended dose level per the assigned DR, they will be replaced before cohort advancement is permitted. Subjects who die before Day 28 of Course 2, and before receiving alternative therapy, and whose death is due to CAR T cell related toxicity will meet the definition of DLT and will not be replaced. Subjects who die before Day 28 of Course 2 due to reasons other than CAR T cell related toxicity and have not experienced a DLT will be replaced before cohort advancement is permitted.

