## **9.9 Cohort Size and Rules for Cohort Advancement**

### **9.9.1 Arms and DLT observation periods**

Subjects will be enrolled onto one of three Arms, as described in Section 5.1.1 Treatment Arm assignment. The first 3 subjects treated will be enrolled only on Arm A or B and will be  $\geq 15$  years and  $\leq 26$  years at time of enrollment. Subjects may be enrolled on Arm C once 3 subjects have been treated on Arm A and/or Arm B, and at least 1 subject on Arm A or B completes Course 2 without experiencing a DLT. Within each Arm subjects will be assigned to successive DRs in Cohorts of up to 3 subjects. Dose escalation rules will be applied separately for each Arm. There will be a  $\geq 7$ -day interval before enrollment of the initial subject onto the other

Arm. [For example, if the initial subject on Arm B is enrolled on 7 July 2018, the initial subject for Arm A cannot be enrolled until  $\geq$  14 July 2018.]

A modified 3+3 statistical design will be used for determining DR assignment with specific details below for determination of a Maximally Tolerated Dose Regimen (MTDR), followed by an expansion cohort. Within each Arm, treatment will begin with DR 1, Course 1. After the first subject completes Course 1 (i.e., completes the seven-day observation period following the last CAR T cell infusion of Course 1) the subsequent 2 subjects may be treated. Subjects within DR1 of each arm may only receive their initial CAR T cell infusion after the previously treated subject completes Course 1. Subjects enrolled in subsequent cohorts may only receive their initial CAR T cell infusion no sooner than 14 days following the date the previously treated subject received their initial CAR T cell infusion. Before the cohorts for the next (higher) DR may open, all 3 subjects of the prior (lower) DR must have received at least 1 of the maximally intended doses in Course 2 and completed a 7-day observation period following the final infusion occurring in Course 2 and not have experienced dose closure as noted below.

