If the current Cohort is fully accrued, receiving therapy, but is not yet completely evaluated for DR DLTs, or if the cumulative number of DLTs at the current DR (including subjects still undergoing evaluation) exceeds 2, then a new subject cannot be assigned to the current DR. Instead, the subject may be offered (a) treatment at the DR below the DR currently being evaluated or (b) to wait until that current Cohort has been completely evaluated to receive treatment in the next DR as per study design. A subject treated under this provision may serve as a member of the current or the next cohort of three at that DR if the trial resumes regular accrual at that same DR or if the trial resumes at the next higher DR but subsequently de-escalates to revisit that DR.

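### The day-7 cut-off for counting DLTs and opening the next dose regimen comes before two of Section 5.2's duration criteria can be settled

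*Protocol*

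**What the plan says.** **The cut-off.** Section 5.2 sets the MTDR count on DLTs that occur "through 7 days following the final CAR T cell infusion received during Course 2". Section 9.5 repeats the window for escalation: "For the purposes of escalation of DR and defining Maximal Tolerated Dose Regimen (MTDR), subjects in the existing cohort will be evaluated for toxicities", starting at the first infusion and ending at the same day-7 mark, or when alternative therapy starts. Under Section 9.9.1 the next DR may open once all 3 subjects have had at least one maximal Course 2 dose and have "completed a 7-day observation period following the final infusion occurring in Course 2 and not have experienced dose closure as noted below".

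**The duration criteria.** Section 5.2 counts related events of Grade 3 or higher as DLTs unless a listed exception applies. In Arm C a Grade 3 neurologic event is excepted if it falls to Grade 2 or lower "within 21 days (treatment with dexamethasone and/or bevacizumab is allowed". For all arms, 5.2 adds any related toxicity lasting more than 14 "days which prohibits the subject from meeting criteria for subsequent CAR T cell infusion". That criterion names no grade.

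**What clearance releases.** Section 5.1.5 caps Arm C DR 1 subjects at DL 1 from Course 3 unless a later DR has been cleared: "In that case, the subject may increase to the highest DL on the subsequent DR". DR 2 and DR 3 have similar provisions.

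**What might make the team wait.** Section 9.9.1 restricts assignment of new subjects while a full cohort "is not yet completely evaluated for DR DLTs". Section 7.9 follows related AEs beyond day 28 to resolution where possible.

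**The concern.** The escalation decision is placed at a time when some of the events it depends on cannot yet be classified. The 21-day exception evidently allows for weeks of treatment: Section 6.4 (Table 6-3) suggests bevacizumab every 2 weeks for up to 2 doses in Arm C, so a second dose comes 14 days after the first. The observation period that feeds the escalation rule is 7 days.

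The gap sits where it matters most. In Arm C DR 2 to DR 4, the regimen's highest dose level is given only in Course 2 among the two courses evaluated for DLTs. Neurologic toxicity soon after that dose is what Arm C needs to detect before going higher. If the count is still provisional when the next DR opens, rules 2a, 2b and 2c of Section 9.9.2 are applied to a number that may change.

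**Working it through.** There is no stated design figure to reproduce. The check is a day count plus a reading of the rules.

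**Inputs.** Day 0 is the final Course 2 infusion received. The cut-off is day 7 (5.2, 9.5, 9.9.1). Onset is day k, with k = 0 to 7. An event that has not resolved is settled on day k + 21 under the Arm C exception. It first exceeds 14 days on day k + 15 under the blocking criterion. It is settled on day k + 7 under the Arm A/B neurologic exception.

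| Criterion | k = 0 | k = 7 | Days after the cut-off |
|---|---|---|---|
| Arm C Grade 3 neurologic, 21 days | 21 | 28 | 14 to 21 |
| Blocking toxicity, more than 14 days, all arms | 15 | 22 | 8 to 15 |
| Arm A/B Grade 3 neurologic, 7 days | 7 | 14 | 0 to 7 |

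So neither of the first two criteria can be settled by day 7 for an event that starts in this window and is still ongoing. The 7-day exception has the same problem in smaller form. Day 28 of Course 2, which 9.5 uses for its replacement rules, does not help. With Week 1 on day 1 and Week 3 on day 15, it falls 28 − 15 = 13 days after the final infusion, short of both 15 and 21.

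**What the rules then do.** Take Arm C DR 3, first cohort, one related Grade 3 neurologic event starting on day 5 and still Grade 3 on day 7. The exception is decided on day 5 + 21 = 26.

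- *Not yet a DLT.* The count is 0/3 and rule 2a escalates to DR 4. If the event is still Grade 3 after day 26, the count becomes 1/3 and rule 2b called for a second cohort first. With two such subjects it becomes 2/3, and rule 2c closes DR 3.
- *A DLT until excepted.* The count is 1/3 on day 7, rule 2b requires a second cohort, and Section 8.1 removes the subject from therapy. If the event improves on day 15, it was one the exception is meant to spare.

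The text does not choose between these readings. The second does nothing for a blocking toxicity below Grade 3. That event becomes a DLT only by duration, on day 15 at the earliest.

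**Dating the event.** If a DLT occurs at onset, the ordinary reading, a late-classified event enters the final count, but the DR may already have opened. If it occurs when the criterion is met, it falls outside the window and never enters the MTDR count.

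**Dose consequence.** DR 3 opens only after DR 2 is cleared, so Arm C subjects in Course 3 or later could already receive DL 2 (2.5 × 10^7). Clearing DR 3 adds DL 3 (5 × 10^7): 5 / 2.5 = 2-fold.

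**New DR 4 subjects.** The stagger in 9.9.1, "no sooner than 14 days following the date the previously treated subject received their initial CAR T cell infusion", would allow starts on days 7 and 21. The first reaches Course 2, and DL 4, no sooner than day 7 + 28 = 35, after the latest classification day of 28.

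**The case against.** The strongest reply is that 5.2 includes every related Grade 3 or higher event unless an exception has been met. An event still Grade 3 on day 7 has not met it, so the cohort stands at 1/3 and any error is conservative. That reading is fair, and a reader should not infer that the protocol plainly scores such a cohort 0/3. But the text does not state it, it empties the 21-day exception for late onsets, and it leaves the blocking criterion untouched below Grade 3.

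The second reply is that the 9.9.1 conditions are minimums, that new subjects wait until the cohort is completely evaluated, that safety is reviewed weekly (9.11.1), and that the Study Chair may close a DR at any time (9.9.3). A careful team could indeed hold. Nothing requires it: 9.9.1 does not define complete evaluation for a pending event, and 9.5 ends the evaluation at day 7.

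The third reply is that a late DLT still counts by onset, that rule 2c closes a DR on 2 or more DLTs in any cohort, and that the MTDR needs at least six evaluable subjects (9.9.4). This stands as far as it goes. A reader might infer that late events are always lost, and the documents do not support that. These rules act after the next DR has opened, however, and do not make the opening wait.

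Other strong inferences also fail:

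- A 5-fold step from DL 1 to DL 3 overstates what clearing DR 3 adds, because DL 2 was already available, and the step is optional.
- Saying that nearly every Arm C Course 2 onset day is undecided assumes the Week 3 infusion is given on schedule during the event. Section 5.1.6 allows a delay of up to 3 weeks, which moves the cut-off too. The count above runs from the final infusion received and does not need that assumption.

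**Conclusion.** The point holds. For toxicity starting 0 to 7 days after the final Course 2 infusion and still ongoing, the day-7 mark comes 14 to 21 days too early for the Arm C neurologic exception and 8 to 15 days too early for the blocking criterion. Following the text either opens the next DR on a provisional count or counts an event the exception was written to spare.

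This is a gap that should be fixed, not one that invalidates the design. It affects only events open at the cut-off. Events that improve before day 7 are unaffected, and Grade 4 or higher neurologic events fall outside the Arm C exception. The plan gives no event rate, so any probability that a cohort's count changes late would rest on an assumed rate, and none is offered here. The conclusion assumes only the time limits in 5.2, 9.5 and 9.9.1 as written.

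**What to change.** Add to Sections 5.2 and 9.9.1:

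*A toxicity with onset up to 7 days after the final Course 2 infusion is counted by its onset date. While a related Grade 3 or higher event that could still meet an exception, or a related toxicity that may block the next infusion, is unclassified, the cohort is not completely evaluated: the next DR does not open, no subject steps up to that DR's dose level, and the MTDR is not estimated.*

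The hold ends at classification, at the latest on day 7 + 21 = 28 after the final Course 2 infusion in Arm C, which matches the overall 28-day DLT window in 5.2. For the blocking criterion the latest day is 7 + 15 = 22.

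The cost is at most 28 − 7 = 21 extra days for a cohort with a pending event and none for other cohorts. No new visits are needed, since AEs are already collected through 28 days after the final infusion (7.9). Cohorts already cleared should be checked once for events that were open at their day-7 mark.

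The amendment should not also make the blocking criterion apply regardless of grade and of the listed exceptions. That would turn a blocking Arm C Grade 3 neurologic event lasting 15 to 21 days into a DLT, which changes the definition instead of repairing the timing.
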